#### Ambulatory EEG (Holter-EEG)

2.3.4

Participants are undergoing a 24-h, 19-channel ambulatory EEG (Micromed Morpheus, 10–20 system). Key parameters:

Bipolar longitudinal montage; sensitivity 10 μV/mm; speed 30 mm/s.Filters: 0.5–70 Hz band-pass, 50 Hz notch.Additional electrooculogram leads for sleep staging.

The conventional 19-channel scalp EEG (international 10–20 system) was selected because it represents the current clinical standard for prolonged ambulatory EEG in patients with cognitive disorders and provides an optimal balance between spatial coverage, patient comfort, recording stability, and feasibility during 24-h outpatient monitoring. While high-density EEG offers improved spatial localization of cortical sources, its practical advantages for prolonged ambulatory recordings remain limited because of increased preparation time, electrode instability, patient burden, and susceptibility to movement artifacts. As the primary objective of the EEG component is the detection and quantification of subclinical epileptiform activity rather than source localization, the standard 19-channel montage is considered appropriate and consistent with previous studies from our group and the broader dementia literature (Horváth et al., 2017, 2018b; Horvath et al., 2021).

The recording bandpass of 0.5–70 Hz was selected to preserve conventional clinical EEG frequencies while minimizing slow baseline drift and high-frequency muscle artifacts. The lower cutoff (0.5 Hz) retains physiologically relevant slow-wave activity required for sleep staging, whereas the upper cutoff (70 Hz) preserves the frequency content of epileptiform spikes and sharp waves while reducing contamination from electromyographic activity. Epileptiform discharges will be defined according to the International Federation of Clinical Neurophysiology recommendations (Kane et al., 2019) as transient spikes or sharp waves with durations of 20–200 ms, followed by an associated slow wave, when present. This definition will facilitate comparison with previous clinical neurophysiology studies and established diagnostic practice.

All recordings will be independently reviewed by two experienced clinical neurophysiologists who are blinded to diagnosis and other clinical information. Epileptiform discharges will be accepted only when both reviewers reach consensus. Prior to consensus adjudication, inter-rater agreement will be quantified using Cohen’s κ coefficient for the presence or absence of subclinical epileptiform activity, with κ values and 95% confidence intervals reported in the final study results. Discordant cases will be reviewed jointly to establish the final classification. Automated spike detection (Persyst) will serve as a supporting tool for quantifying spike density, amplitude, and duration, while all final classifications remain based on expert visual assessment. The average spike density (spikes/hour) will be computed, and scalp distribution will be categorized (frontal, temporal, parietal, occipital, etc.) using Micromed SystemPLUS 98. Participants will be labeled as EEG-positive or negative for SEA relative to HC normative values obtained from our reference database (ACOL). The SEA detection pipeline is reported in our previous publications (Horváth et al., 2018b; Horvath et al., 2021).

#### CSF and blood biomarkers

2.3.5

All participants will provide blood samples for plasma biomarkers. MCI participants undergoing clinically indicated lumbar puncture will provide CSF samples. Samples will be stored at -80°C and analyzed using validated ELISA assays for:

Aβ40, Aβ42.Total tau (t-tau).Phospho-tau181 (p-tau181).

CSF biomarkers will be interpreted in the context of AD-related pathology; blood biomarkers will support mechanistic analyses and may inform future non-invasive stratification (Bouwman et al., 2022).

### Study protocol for mechanistic in-ward testing

2.4

#### Participant selection and extraction of normative values

2.4.1

Across all groups (HC, MCI, ASD, ADHD), participants with clear evidence of cortical hyperexcitability—defined by at least one of: SEA on EEG above a predefined density threshold; or fMRI-defined hyperactivity in DMN/SN/AN—are invited to participate. We will initially prioritize HC and MCI subjects during the pilot phase to refine the in-ward protocol, then extend to ASD/ADHD.

Normative values for the fMRI and EEG metrics will be calculated using the ACOL dataset. The ACOL dataset is our clinical registry, founded in 2014, and contains longitudinal data from 500 individuals at various stages of the cognitive continuum. The dataset includes 280 healthy individuals (mean age = 55) with records on clinical anamnesis, demographics, blood-based biomarkers, neurological examination, medications, neuropsychology, 24-h Holter-EEG, 10-min resting EEG, sMRI, 10-min resting fMRI, pupillometric data, fine-movement analysis, and autonomic functions. All participants have been scanned with the same MRI scanner (Siemens Magnetom 3T) and examined with the same EEG recording system (Micromed Morpheus Holter-EEG). Further details on the dataset can be found at the EuroFingers Consortium website^1^.

To generate normative fMRI values, we perform rigorous preprocessing of all scans—motion correction, spatial normalization, smoothing, and signal denoising—to ensure comparability across individuals. Next, functional metrics, including functional connectivity strength, regional homogeneity (ReHo), amplitude of low-frequency fluctuations (ALFF), Hurst-exponent, and network efficiency, are extracted for each subject. Within the healthy control group, these measures are then aggregated and standardized by computing the mean and standard deviation of each metric across all participants to generate z-score distributions that define the “normal” range. Statistical modeling (Gaussian mixture) is used to identify normative intervals and detect outliers. To account for biological variability, the dataset is stratified by relevant covariates such as age, sex, and head motion. The resulting normative models can then serve as a statistical reference framework, allowing patient metrics to be expressed as deviation scores (z-scores) that quantify brain abnormalities relative to typical controls.

To generate normative EEG values, we perform meticulous EEG preprocessing on 24-h recordings—artifact removal (e.g., eye blinks, muscle noise), filtering, and referencing—to ensure clean data. Two manual expert reviews of the files to identify potential SEA in line with the previously published protocols (Kamondi et al., 2024; Port et al., 2019). To define normal limits, the density, amplitude, duration, and spatial distribution of these events can be quantified across all control recordings. Statistically, normal values are represented by upper tolerance limits (the 95th percentile) of spike density (events per hour) computed from the control group. Normative modeling is applied to further refine these thresholds by accounting for age, sex, sleep state, and recording montage, variables known to influence EEG background and transient patterns. Additionally, spectral power and band ratios (delta, theta, alpha, beta, gamma) are used to construct normative baselines, against which epileptiform spikes produce transient deviations.

#### In-ward protocol

2.4.2

Participants will be admitted to a dedicated video-EEG monitoring unit for three consecutive days and nights.

Continuous video-EEG: 34-channel scalp EEG (Micromed Morpheus, 10–20 system) will be recorded throughout admission, with peri-orbital leads for sleep staging.Memory paradigms: Three parallel versions of the RAVLT will be administered on consecutive evenings (7 pm).○Immediate recall (five learning trials) and delayed recall at 30 min.○Morning recall at ∼9 am to assess overnight retention.

Sleep analysis:○Visual staging of 20-s epochs according to AASM criteria (Moser et al., 2009).○Artifact annotation in 4-s segments.○Automated slow and fast spindle detection with Individual Adjustment Method (Bódizs et al., 2009).○Quantification of spindle density, duration, amplitude, and frequency over frontal (slow spindles) and centro-parietal (fast spindles) leads, in N2 and N3, and combined N2+N3.○Power spectral analysis of N2 and N3 for slow-wave sleep characteristics.Serial blood sampling: Evening and morning samples across the 3-day stay to estimate circadian patterns of plasma tau and Aβ.

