#### Neuropsychological assessment

2.3.1

Neuropsychological testing (Hungarian language versions) will be performed by trained neurologists or neuropsychologists using a unified UDS3-based battery (Boccardi et al., 2022). Instruments include:

Global cognition: Addenbrooke Cognitive Examination–Revised (ACE-R), Mini-Mental State Examination (MMSE).Memory and learning: Rey Auditory Verbal Learning Test (RAVLT: Sum of first five trials [Sum5], delayed recall after 30 min [Trial 7]).Attention and executive functions: Trail Making Test A (TMT-A: processing speed) and B (TMT-B: set-shifting).Visuospatial and constructional skills: Benson Figure Copy (immediate copy and delayed recall).Working memory: Number Span Backward (NSB).Language: Category (semantic) and phonemic verbal fluency.Mood and anxiety: Beck Depression Inventory-II (BDI-II), Spielberger State and Trait Anxiety Inventory (STAI-S, STAI-T).

Cut-offs for normal performance (e.g., MMSE > 25, age- and education-adjusted norms) will be applied for diagnostic purposes and covariate control. This battery has been validated and widely used by our group in previous cohorts (Berente et al., 2022; Csukly et al., 2016; Csukly et al., 2024; Unoka et al., 2026).

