#### Data extraction and mechanistic analyses

2.4.3

For each participant, we will derive:

SEA density and temporal distribution across nights and days.Within-subject variability in RAVLT learning, 30-min retention, and overnight consolidation.Sleep architecture metrics and spindle parameters.Day–night and day-to-day changes in plasma tau/Aβ.

SEA density will be correlated with memory performance, spindle metrics, and biomarker levels, as assessed using mixed-effects models that account for repeated measures. Comparisons will be made between SEA-rich and SEA-poor epochs and between days with high vs low hyperexcitability burden. Group-specific patterns (e.g., MCI vs ASD vs ADHD) will be examined.

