#### Mechanistic analyses

2.6.2

Linear mixed-effects models will relate within-subject variation in SEA density to RAVLT performance, sleep spindle parameters, and plasma tau/Aβ levels, with random intercepts for participants.Connectivity changes (morning vs evening, SEA-rich vs SEA-poor epochs) will be assessed with paired tests and network-based statistics.Mediation models will explore whether sleep spindle disruption mediates the effect of SEA on overnight memory consolidation.

Effect sizes, confidence intervals, and model diagnostics will be reported systematically.

The entire analysis pipeline is highlighted in Figure 2.

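### The in-ward memory model names no term for night or test form, so order effects over three nights can be confounded with the effect of epileptiform activity

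*Protocol article*

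**What the plan says.** In-ward protocol (2.4.2) sets the stay: "Participants will be admitted to a dedicated video-EEG monitoring unit for three consecutive days and nights". On memory testing it says "Three parallel versions of the RAVLT will be administered on consecutive evenings (7 pm", with five learning trials, a 30-minute delayed recall, and then "Morning recall at ∼9 am to assess overnight retention". It gives no order or rotation of the forms and no adaptation night. The same test has already been used in the main battery (Neuropsychological assessment, 2.3.1): "Memory and learning: Rey Auditory Verbal Learning Test (RAVLT".

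Mechanistic analyses (2.6.2) states the model: "Linear mixed-effects models will relate within-subject variation in SEA density to RAVLT performance", and also to spindle parameters and plasma tau and amyloid, "with random intercepts for participants". No other model term is named. Data extraction and mechanistic analyses (2.4.3) describes the same associations "as assessed using mixed-effects models that account for repeated measures" and adds a contrast "between days with high vs low hyperexcitability burden". Adjustment for the order of the days is not mentioned there either.

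Sample size justification (2.2.4) presents within-person relationships as the main purpose of the substudy. It labels mediation and diagnostic-subgroup analyses as exploratory; the main SEA–memory model is not on that list.

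**The concern.** With only three nights per person, several things can change from the first to the third. Memory scores can move through general task practice, interference from earlier lists, or forms of unequal difficulty. Sleep can change as the patient gets used to the ward and the electrodes. SEA density can change with sleep: the article itself treats sleep EEG as sensitive for epileptiform activity (Rationale, 1.1) and lists sleep state among the influences on EEG transients (2.4.1).

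A random intercept does not remove a movement common to all participants. If memory and SEA both move, the within-person slope picks up the shared movement. Memory improving while SEA rises would look as if SEA were harmless or helpful, and could mask real harm. Memory falling while SEA rises would look like harm and appear to confirm Hypothesis 7. If all participants receive the forms in the same order, form is also completely aliased with night, and no later analysis can separate the two.

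**Working it through.** **Substudy size.** Section 2.2.4 expects about 45 eligible participants and about 40 after 20% attrition. 0.15 × 300 = 45, although 300 includes the controls. 45 × (1 − 0.20) = 36, not 40. That mismatch is a separate matter; here both 36 and 40 are used.

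**How the bias arises.** Let memory shift by *m* and SEA by *s* per night (linear pattern −1, 0, +1), with no true SEA effect and SEA in units of its within-person SD. Per person, the shared cross-product over three nights is 2*ms*, and the expected within-person sum of squares of SEA is 2 + 2*s*². The spurious within-person slope is therefore *ms* / (1 + *s*²). It is zero if either shift is zero.

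- *m* = 1 word, *s* = 0.5: 0.5 / 1.25 = 0.40 words per SD of SEA.
- *m* = −1 word, *s* = 0.5: −0.40.

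**Simulation 1 (words).** Within-person regression, residual SD 1.5 words, 2,000 studies per scenario, two-sided 5%. All drifts are assumed.

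- 1 word and 0.5 SD per night (memory 1/1.5 = 0.67 SD): rejection 56% at n = 36 and 61% at n = 40; slope +0.40.
- −1 word and 0.5 SD: 58% at n = 36; slope −0.40.
- 0.5 word and 0.3 SD: 10% at n = 36.
- With night as a categorical fixed effect: 4–6% in all scenarios.

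**Simulation 2 (SD units).** Random-intercept model fitted by feasible generalised least squares, intraclass correlation 0.6 assumed for both series, 2,000 studies per cell. False-positive rate without a night term:

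| Assumed shift, memory / SEA (SD) | n = 36 | n = 40 |
|---|---|---|
| None | 5.4% | 5.7% |
| Per night, 0.5 / 0 | 5.7% | 4.7% |
| Per night, 0 / 0.5 | 5.2% | 5.6% |
| Per night, 0.25 / 0.25 | 8.3% | 7.1% |
| Per night, 0.5 / 0.25 | 11.8% | 13.1% |
| Per night, 0.5 / 0.5 | 28.5% | 32.4% |
| Per night, 0.5 / −0.5 | 30.0% | 33.9% |
| Per night, 1 / 0.5 | 56.9% | 59.9% |
| Per night, 1 / 1 | 97.8% | 98.6% |
| First night only, 0.25 / 0.25 | 5.6% | 5.9% |
| First night only, 0.5 / 0.5 | 8.6% | 9.0% |
| First night only, 1 / 0.5 | 17.3% | 17.3% |
| First night only, 1 / 1 | 44.2% | 46.8% |

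With a categorical night term the rate was 4.2% to 6.7% in every cell and the mean bias was about zero. The slopes here are smaller than the formula gives (0.5 / 0.5 at n = 40: 0.14 against 0.25/1.25 = 0.20). SEA was entered uncentred, so the estimate mixes the within-person slope with a between-person slope of zero.

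**If only memory drifts.** The test is valid but less precise. At 1 word per night the within-person residual sum of squares rises from 2 × 1.5² = 4.5 to 4.5 + 2 × 1² = 6.5 per person, so the standard error rises by a factor of √(6.5/4.5) = 1.20.

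**The case against.** The strongest reply is that this argues from silence. The sentence in 2.6.2 is a summary: it names predictor, outcomes and random part, and no covariates at all. A night term is not excluded, and form order may sit in a testing manual. That stands, so a reader who infers that the investigators have ruled out a night term goes beyond the text. Still, the one structural feature the article states does not deal with a shared night shift, and form order is fixed when the data are collected.

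A reader might also infer that order effects will necessarily be taken for SEA effects. The documents do not support this. Both series must shift, no night-to-night trend in SEA is reported, and a shift in one series alone leaves the test near 5%. Nor do they say that the form order is common to all or that the baseline list is reused.

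Other points carry weight. Parallel forms already limit item-specific practice. Hypothesis 7 concerns retention and overnight consolidation; scored as change within a list, practice and list difficulty act on both recalls and partly cancel. The simulations drift the score itself, so they overstate the effect for such outcomes. Practice and form difficulty cannot affect plasma markers; only a night effect could, and neither plasma nor spindle outcomes were simulated. Section 2.4.1 plans a pilot phase to refine the in-ward procedure, and 2.2.4 partly frames the substudy as effect-size estimation. That framing does not remove the problem: a confidence interval around a confounded slope is centred on the wrong value.

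**Conclusion.** The point holds as a possible confounding that the stated design and model leave open. Run as written, the model does not separate night order from SEA if memory and SEA both shift systematically over the stay, and the error could go in either direction. Its size is unknown because the documents give no drift figures. Under the assumptions above, the false-positive rate at n = 36–40 is about 7–13% for mild drift or a moderate first-night-only shift, and about 55–60% for memory at about 0.7–1 SD with SEA at 0.5 SD per night. A small first-night-only shift leaves it close to nominal. The upper figures should not be read as the expected error rate: nothing in the documents selects that scenario. Outcomes scored as retention within a list would be affected less. It remains worth correcting because this is the substudy's main within-person analysis and the remedy is standard and cheap.

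**What to change.** In 2.4.2, rotate the order of the three forms across participants (for example ABC, BCA, CAB) and use forms other than the baseline list. In 2.6.2, add night (categorical, three levels) and form as fixed effects to the mixed models with RAVLT as outcome, and night to those for spindle and plasma outcomes. Report the model without night as a sensitivity analysis.

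Under a common form order, the night term alone already protects the SEA slope, because it absorbs night and form together. Rotation is what allows the two to be separated. The night term can also be applied to participants already tested; rotation can start with the next admission.

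The cost is a rotation list for the testers, a line of analysis text, and up to 4 degrees of freedom (2 for night, 2 for form) out of 36 × 2 = 72 to 40 × 2 = 80 within-person ones. There is also a real trade-off: the night term removes any SEA variation that all participants share from night to night, part of which may be of interest. The sensitivity analysis shows how much the result depends on it.

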**Methods:**

In a prospective, multimodal observational study, we are recruiting 75 participants per group (patients with mild cognitive impairment, patients with autism spectrum disorder, patients with attention deficit/hyperactivity disorder, and healthy controls; total *N* = 300) at the National Institute of Psychiatry and Addictology (Budapest, Hungary). All participants are undergoing a harmonized diagnostic protocol including detailed neuropsychological assessment, structural MRI, resting-state functional MRI, and 24-h ambulatory electroencephalography. Patients with neurodegenerative conditions will additionally undergo CSF sampling. Individuals who exhibit markers of cortical hyperexcitability will be invited to an in-ward mechanistic substudy (3-day video-electroencephalography monitoring with repeated neuropsychological paradigms, overnight sleep recordings, and spindle analysis, and serial blood sampling to characterize circadian dynamics of tau and amyloid.

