Beyond AD, SEA and other markers of cortical hyperexcitability are reported in ASD and ADHD, where they may relate to attentional deficits, learning problems, and behavioral disturbances (Lee et al., 2016; Spence and Schneider, 2009). Functional MRI studies in these populations describe hyperactivity and altered connectivity within key large-scale networks, including the default mode network (DMN), salience network (SN), and attention networks (AN), particularly early in the disease course (Hull et al., 2017; Konrad and Eickhoff, 2010). Some recent observations also suggest that the observed hyperactivity and connectivity changes may reflect an early excitatory/inhibitory (E/I) imbalance in preclinical AD (Fortel et al., 2023; Li et al., 2025; Ranasinghe et al., 2025). Based on these reports, some authors propose that multilevel changes in neural networks may be associated with a very early shift in E/I balance, a feature of AD pathology (Stam et al., 2023). A similar link between hyperactivity and hyperexcitability has been proposed in ASD (Port et al., 2019) and ADHD (Mamiya et al., 2021). However, disease-specific spatial differences in E/I imbalance have also been proposed as the primary involvement of the prefrontal cortex in ASD and ADHD (Ajram et al., 2017), and the DMN-specific imbalance in preclinical and prodromal AD (Giorgio et al., 2024). These commonalities suggest that ASD and ADHD may represent early-life manifestations of circuit-level dysregulation, while Alzheimer’s reflects its late-life degeneration (Pievani et al., 2011).

Despite this emerging evidence, several major knowledge gaps remain (Kamondi et al., 2024; Vossel et al., 2026): 1) There is no systematic, multimodal characterization of SEA and fMRI hyperactivity across MCI, ASD, ADHD and healthy aging within a unified protocol; 2) It is unclear to what extent hyperexcitability markers predict domain-specific cognitive impairment and neurodegeneration (atrophy, white matter damage); 3) The relationship between hyperexcitability, large-scale functional connectivity, sleep structure, sleep spindles, and memory consolidation is poorly understood; 4) Whether hyperexcitability modulates the burden or circadian dynamics of tau and amyloid-β pathology, particularly in prodromal AD, is unknown.

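### Evening and morning blood draws support a diurnal change in plasma tau and Aβ, not the circadian pattern the in-ward substudy says it will estimate

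*Protocol article*

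**What the plan says.** The protocol article gives the in-ward blood sampling a circadian purpose in two places and motivates it in a third:

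- Abstract, Methods: "serial blood sampling to characterize circadian dynamics of tau and amyloid".
- Section 2.4.2: "Evening and morning samples across the 3-day stay to estimate circadian patterns of plasma tau and Aβ".
- Section 1.1, the fourth knowledge gap: "Whether hyperexcitability modulates the burden or circadian dynamics of tau and amyloid-β pathology, particularly in prodromal AD, is unknown". The same section ends by saying that the paper sets out a design to address the listed gaps.

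The sampling is limited to evenings and mornings of a stay described as "Participants will be admitted to a dedicated video-EEG monitoring unit for three consecutive days and nights". No other in-ward draw time is given, and neither are the clock times of the draws.

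Section 2.4.3 then lists what will be derived from the samples: "Day–night and day-to-day changes in plasma tau/Aβ". Section 2.6.2 relates plasma levels to SEA density with linear mixed models that have participant random intercepts. It names no time-of-day, harmonic or phase term. The limitations in section 3.5 cover the restriction of CSF sampling and the enrichment of the substudy, but not this point.

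**The concern.** The stated purpose and the sampling do not fit each other. A circadian pattern is a curve over 24 hours, and describing even its simplest form requires a level, an amplitude and a peak time. Two times of day give two points on that curve. More days add replicates of those two points, and more participants sampled at the same two times add none either. This is a property of the sampling itself, so no analysis plan can recover the missing information later.

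What is at stake is interpretation. If the evening-morning difference is reported as the circadian dynamics of tau or amyloid, a person or group whose rhythm merely peaks at a different hour could be described as having a weaker, absent or reversed rhythm. Section 2.4.3 says that patterns specific to MCI, ASD and ADHD will be examined, so such a comparison is foreseeable.

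A related point concerns the mixed model. Both SEA density and plasma concentration may vary with time of day; section 1.1 notes that sleep EEG is particularly sensitive for detecting epileptiform activity in dementia. A model that pools evening and morning samples without a term for time of draw can attribute a shared day-night difference to an SEA-plasma association.

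**Working it through.** The article gives no precision or power figure for this purpose, so there is none to reproduce. The check is whether the rhythm can be identified from the planned samples.

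**Inputs**

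- Two times of day, evening and morning, over three days (section 2.4.2). I take this as six samples; the article gives no count.
- Draw times are not stated. I assume 19:00 and 09:00, borrowed from the memory testing in the same section, where learning is at 7 pm and the next step is "Morning recall at ∼9 am to assess overnight retention". The rank result does not depend on this choice.
- Model: a single 24-hour cosine, y(t) = M + A·cos(2π(t − φ)/24), with level M, amplitude A and peak time φ. This model is mine, chosen as the simplest description of a circadian pattern; the article names none.

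**Step 1: rank.** In linear form the design row at time t is [1, cos(2πt/24), sin(2πt/24)]. Two clock times give two distinct rows, so the rank is at most 2 for three parameters. Computed for six samples over three days:

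- 19:00/09:00: rank 2.
- 20:00/08:00: rank 2.

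For draws exactly 12 hours apart, the mean of the two values does recover M, because the cosine terms cancel. A and φ still cannot be separated.

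**Step 2: different rhythms, same data.** Each rhythm below gives 10.97 at 19:00 and 9.03 at 09:00:

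| M | A | Peak |
|---|---|---|
| 10.00 | 1.000 | 20:00 |
| 9.85 | 1.155 | 18:00 |
| 10.26 | 1.414 | 23:00 |
| 9.55 | 2.000 | 16:00 |

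For the last row: 9.552 + 2·cos(45°) = 9.552 + 1.414 = 10.966, and 9.552 + 2·cos(105°) = 9.552 − 0.518 = 9.034. A twofold difference in amplitude leaves no trace in these samples.

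**Step 3: same amplitude, different contrast.** At 19:00 and 09:00, evening minus morning equals A·[cos(2π(19 − φ)/24) − cos(2π(9 − φ)/24)]:

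| Peak φ | Evening − morning |
|---|---|
| 20:00 | +1.93A |
| 18:00 | +1.67A |
| 16:00 | +0.97A |
| 14:00 | 0 |
| 11:00 | −1.37A |
| 08:00 | −1.93A |

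A shift in timing alone can shrink, remove or reverse the contrast.

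**Step 4: would irregular draw times help?** If the six draws vary uniformly by ±1 hour around 19:00 and 09:00, the rank becomes 3 but precision is very poor. With σ the residual SD, the worst-determined direction has a median standard error of 3.7σ (5th to 95th percentile 2.5σ to 7.5σ; 5,000 simulated schedules). Six samples every 4 hours would give 0.58σ. Incidental variation in timing is no practical remedy.

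**The case against.** The strongest reply is that the operational plan is already sound. None of the eight hypotheses in section 1.2 mentions a circadian pattern; Hypothesis 6 concerns tau and amyloid levels, as does the matching secondary outcome. Section 2.4.3 derives day-night and day-to-day changes, which these samples can estimate. No planned analysis estimates amplitude or phase, so the three-parameter model comes from this review. On that view the matter is loose wording in an abstract clause, a gap statement and one procedural item.

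Much of this stands. The data are usable, and no numbered hypothesis or listed outcome fails. It does not remove the point, because sections 2.4.2 and the abstract state what the sampling is for, and the sampling cannot do it. Any reasonable model of a 24-hour rhythm needs at least these three quantities.

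A reader might go further and infer that phase differences will appear as amplitude differences between MCI, ASD and ADHD. The documents do not support that. Nothing in them says that biomarker peak times, or sleep timing, differ between the groups. Section 2.2.4 also treats subgroup comparisons across diagnoses as exploratory with limited power, and describes the substudy as mainly within-subject. A stable difference in phase between people does not by itself bias comparisons within a person at the same clock time.

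It can also be said that recording draw times and choosing covariates belong in SOPs or an analysis plan, which are not shown. That is fair: their absence from the article is not counted as an error here, and the covariate is recommended only because the article's description of the model names no such term.

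**Conclusion.** The point holds in limited form. The abstract and section 2.4.2 claim a circadian purpose that evening and morning samples cannot serve: rank 2 for three parameters, for any two fixed clock times and any number of days. What can be estimated is the evening-to-morning change and its day-to-day variation, which section 2.4.3 already derives. The fourth gap in section 1.1 is therefore addressed for diurnal change only.

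The contrasts of +1.93A to −1.93A and the twofold amplitude example show what cannot be distinguished. They are not estimates of error in this study, since they rest on assumed draw times and hypothetical peak times, and the documents give no rhythm amplitude or spread of peak times for tau or Aβ. Misreading phase as rhythm size is conditional on peak times differing and on the day-night change being read as the size of the rhythm. It would mainly affect the exploratory between-group comparisons.

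**What to change.** 1. In the abstract and section 2.4.2, replace the circadian purpose with evening-to-morning (diurnal) change and day-to-day variability in plasma tau and Aβ, to match section 2.4.3.
2. In section 3.5, state that amplitude and phase cannot be separated from two times of day, so the fourth knowledge gap is addressed only for diurnal change.
3. In the section 2.6.2 mixed model for plasma levels, include time of draw, as morning/evening or as actual clock time, so that the SEA-plasma association is not confounded with time of day. Time since sleep offset, available from the planned sleep staging, is optional. Neither covariate makes phase identifiable.

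The cost is a narrower claim, some rewording and one covariate. No extra samples are needed. Keeping the circadian claim instead would require at least three well-spaced clock times per day, which is a larger change to the substudy.
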